The development of the iron-containing beads is novel on-going research and consequently the preparation of the iron-containing alginate beads imposes certain limitations on the proposed study design. Currently, iron incorporation into the alginate beads is within 15% of that predicted. Analysis of the iron (atomic absorption spectroscopy) incorporated into the alginate beads is a three day procedure, and long term storage method for the beads has not yet been established. These limitations mean that the sequence of the test meals cannot be randomised (Fig.1). Iron containing alginate beads will be prepared for each volunteer approx. 48 hours before the test meal and stored in a refrigerator in a food grade kitchen at 4°C. Sub-samples of each batch of beads administered to each volunteer will be collected and their iron content analysed using atomic absorption spectroscopy. Once the exact content of iron present in the beads administered to each specific volunteer in Test meal 1 and 2 is known (and recorded), exactly the same amount of ferrous

gluconate will be weighed into a capsule and administered to that volunteer in a subsequent test meal (Test meal 4 and 3 respectively) after a minimum 7 day wash-out period.

For each test meal an oral dose of iron (approximately 20mg), sufficient to perturb the normal serum iron concentration, will be given to apparently healthy adult volunteers after a 10 hour (overnight) fast.

All test meals will be prepared by a trained (holding a level 2 award in food safety in catering) member of the scientific staff in the Clinical Research Trial Unit kitchen. The four test meals will be as follows:

- Test meal 1 for all volunteers (group A and B): 200ml cola jelly prepared from 200ml cola (Coca-Cola), 10ml of commercially available Diet Cola flavoured Drink Concentrate (Sodastream, Lakeland) and gelatine ([name]) gelatine (from animal source, [name], UK) with the addition of ferrous gluconate (approx 20mg +/- 2mg) in alginate beads (approx. 22.2g) followed by 200ml of diet cola drink (Coca Cola) with 3 placebo capsules (filled with 50mg commercially available dextrose powder, 'Glucose Dextrose Powder', PharmacyNearU.com) acting as placebos for calcium and an iron capsules.)

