- Test meal 2 for 8 volunteers only (group A): 200ml cola jelly prepared from 200ml cola (Coca-Cola), 10ml of commercially available Diet Cola flavoured Drink Concentrate (Sodastream, Lakeland) and gelatine (from animal source, [name]) with the addition of ferrous gluconate in alginate beads followed by 200ml of a diet cola drink (Coca Cola) with 2 commercially available capsules containing calcium phosphate, (Freeda vitamins, USA) (300mg of calcium in each capsule, in total 600mg of calcium) and one placebo capsule in place of the iron capsule.
- Test meal 3 for 8 volunteers only (group A) : 200ml cola jelly prepared as above without iron containing alginate beads(approx. 22.2g), 2 calcium capsules (as above) and 1 ferrous gluconate capsule (prepared exclusively for each volunteer to match the iron content in the alginate beads administered in test meal 2) followed by 200ml diet cola drink.

- Test meal 4 for all volunteers (group A and B): 200ml cola jelly prepared as above, 1 ferrous gluconate capsule (prepared exclusively for each volunteer to match the iron content in the alginate beads administered in test meal 1) followed by two dextrose (50mg of dextrose in each capsule) placebo capsules in place of the calcium capsules and 200ml of diet cola drink.

[figure not shown]

Figure 1. Study design

All appointments which volunteers will attend to (starting from initial interview through the screening and test visits) will take place in Clinical Research and Trials Unit (CRTU) based in the Norwich Medical School at the University of East Anglia. The CRTU provides all the required facilities and resources for performing human trials.

A trained nurse based in the CRTU will undertake the following clinical procedures. On each test meal day an intravenous (i.v.) cannula will be inserted into an appropriate peripheral vein in one of the volunteer's arms. The cannula will remain in situ for six hours. A baseline blood sample will be taken prior to consuming the test meals. Further blood samples (5ml each time) will then be taken 20, 40, 60, 80, 100, 120, 150, 180, 240, 300 and 360 min after ingestion of the test meals (described above) and collected into appropriate tubes for the preparation of serum. Serum iron concentrations will be measured in each sample using a colorimetric assay. Figure 2 provides a flow chart of the study outline.

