### **1.2.2. Study Population**

Volunteers will be recruited from a target population of women of child-bearing age (18-45y) and men who are regular blood donors (18-65y) as these individuals generally have iron stores at the lower end of the normal range. Iron absorption is more efficient when ferritin stores are below  $<60\mu\text{g/L}$  and therefore this will maximize the sensitivity of the absorption test.

Female volunteers who decide to take part in the study will be asked by a study scientist at the start of each experimental day if they are menstruating and if they are not, then they will be asked how many days ago menstruation has completed. This information may help to explain potential fluctuations in ferritin levels and potential differences in iron appearance in the serum during different experimental days. Menstrual iron losses may affect biomarkers of iron status such as ferritin which may in turn affect iron absorption.

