Volunteers will be excluded if their BMI is <18.5 and >30 or their blood pressure measurements are >160/100. Volunteers will also be excluded from further participation if the serum ferritin is less than 15ug/L (indicates iron deficiency) or greater than 60µg/L (The full list of inclusion / exclusion criteria are given in section 7)

Blood screening results will be examined by an experienced CRTU nurse who will advise the study scientist if all screening parameters are within the normal range for sex and age, and therefore whether the participant can take part in the study. In addition, screening results will be forwarded to the volunteers G.P. If any of the parameters (apart from ferritin values of  $\geq 15 \leq 60 \mu\text{g/L}$ , study specific requirement) fall outside the normal range the results will be forwarded to the study medical advisor [name], UEA. [name] will then be contacted by a study scientist and asked whether the results could affect the study data or have implications for the health of the volunteer, and therefore whether inclusion, exclusion or re-screen is appropriate.

The GPs of those successfully recruited onto the study will be informed of their patient's participation in the study by letter (Annex 7) and will be sent copies of all clinical screening results (Annex 8, Annex 9). If the CRTU nurse advises the study scientist that blood screening results are abnormal, the volunteer will be asked to contact their G.P. Volunteers will be informed of flagged blood results by a telephone call and letter (Annex 11) advising them to speak to their GP to discuss the results. Non-clinical study scientists will not discuss clinical results with individual volunteers. All abnormal clinical results obtained during the study from fresh samples (not stored), that have been analysed at an accredited laboratory and which fall outside the standard reference ranges, will also be sent to the GP (Annex 10).

The volunteer will agree to this information being sent to the GP by signing the consent form.

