## **7. Inclusion / Exclusion Criteria**

The Inclusion Criteria for this study are:

- Apparently healthy women (aged 18-45) or male blood donors (aged 18-65)
- Serum ferritin value of  $\geq 15 \leq 60 \mu\text{g/L}$

- BMI >18.5 or < 30
- Willingness to consume jelly prepared with the use of gelatine from an animal source

The exclusion criteria for this study are:

- Diagnosed with a long-term illness requiring active treatment, e.g. diabetes, cancer, cardiovascular disease
- Currently smoking or stopped smoking in the last 12 months
- Previous or current GI disease
- Any significant co-morbidity
- Previous GI surgery
- Blood donation within the previous 3 months assuming that volume taken is above 500ml in a 4-month period
- Blood transfusion within the last 3 months
- The results of the screening tests indicate unsuitability to take part in the study
- Related to someone in the study team i.e. spouse, partner or immediate family member
- Regular prescribed medication that may interfere with iron metabolism
- Regular use of antacids and laxatives (at least once a week)
- Women who are pregnant or less than 12 months since giving birth
- Women who are breast feeding
- Vitamin supplements with or without minerals if taken more than once a week, and unwillingness to discontinue occasional use for the duration of study
- Unwillingness to discontinue use of herbal supplements for the duration of study
- Unwillingness to consume jelly prepared with animal source gelatine
- Use of antibiotics within four weeks prior to study start

- Parallel participation in another study which involves dietary interventions or sampling of blood that may increase the volume taken above 500ml in a 4-month period
- Asthma requiring treatment within the last two years
- Results of clinical screening which indicate a health problem which could compromise the well-being of the volunteer if they participated or which would affect the study data.

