## **8. Study Procedures**

### Randomization

Volunteers will be assigned randomly to group A or B and they will be asked to complete up to 4 study days (4 in group A and 2 in group B). Volunteers will be unaware that if they were randomly assigned to group A it will result in completing 4 study days and that if they were assigned into group B it will result in completing 2 study days. Maintaining volunteers' unawareness will improve flexibility of pairing them for experimental days. After completing 2 study days, volunteers from group B will be contacted, thanked for their involvement and informed that their participation in the study is complete as all the required data have been collected. The PIS will contain details advising potential study participants that they will be randomly selected to take part in either two or four study days.

Randomization will be undertaken by a third party unconnected with the study using the randomization generator available at the [www.randomization.com](http://www.randomization.com) website. Randomisation will be generated for 16 sequential volunteers, and each random sequence generated will be placed in order in a sequentially numbered opaque, sealed envelope (1-16). As each volunteer is recruited onto the study, the appropriately numbered envelope will be opened by the study scientist to reveal the assignment to the group A or B. Note the study is single-blinded so the participants will be unaware to which group they will be allocated and which test meal they will be receiving on each experimental day.

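### The donation exclusion looks back 3 months to enforce a 500 ml per 4-month limit and does not say that study blood counts, so a donor at 3 to 4 months can be admitted and then pass the limit

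*Protocol*

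**What the plan says.** Section 7 of the protocol excludes "Blood donation within the previous 3 months assuming that volume taken is above 500ml in a 4-month period". One clause thus carries two periods: 3 months for the donation and 4 months for the volume. It does not say which blood makes up the volume, and it gives no date from which the 3 months run. The antibiotic criterion in the same list does have an anchor: "Use of antibiotics within four weeks prior to study start".

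The same limit appears again in section 7 for parallel studies. That criterion rules out another study with "sampling of blood that may increase the volume taken above 500ml in a 4-month period". It has no 3-month look-back.

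Section 1.2.2 recruits "men who are regular blood donors (18-65y) as these individuals generally have iron stores at the lower end of the normal range", and section 7 admits men only if they are blood donors.

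On study blood, section 6.2 takes 10 ml at screening. Section 1.2.1 takes a baseline sample on each test day, then: "Further blood samples (5ml each time) will then be taken 20, 40, 60, 80, 100, 120, 150, 180, 240, 300 and 360 min". Section 8.1 confirms 5 ml for the baseline sample too. Under section 8, group A has four test days and group B two. The protocol states no total study blood volume.

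**The concern.** A 4-month limit cannot be enforced by asking only about the last 3 months. If the volume is a running total, a volunteer who donated within 3 months is caught whenever the total would pass 500 ml. A volunteer who donated between 3 and 4 months ago does not meet the first half of the clause, so the volume is never considered. Yet that donation is still inside the 4-month period when the first study samples are drawn.

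The protocol sets the 500 ml limit twice, and every man in the trial must be a donor, so this line helps decide which men enter and when. What is at stake is adherence to the protocol's own blood-volume limit and consistent application of the criterion by different staff. Sample size, test and treatment comparison are not at stake.

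**Working it through.** **Inputs from the protocol**

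- Screening sample: 10 ml (section 6.2).
- Test day: 1 baseline + 11 later samples = 12 samples of 5 ml, so 12 × 5 = 60 ml (sections 1.2.1 and 8.1).
- Test days: 4 in group A, 2 in group B, at least 7 days apart (sections 8 and 8.1).

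The protocol states no total to reproduce. By arithmetic:

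- Group A: 10 + 4 × 60 = 250 ml.
- Group B: 10 + 2 × 60 = 130 ml.

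**Assumptions, not in the protocol**

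- One donation of 450 to 500 ml. The thresholds below let the reader use another volume.
- 30-day months, so 3 months = 90 days and 4 months = 120 days.
- The 3 months are counted back from screening, where eligibility is assessed.
- Test days exactly 7 days apart.
- Visit 3 no earlier than day 3 after screening. Section 6.2 says "Blood screening results will be examined by an experienced CRTU nurse" and section 1.2.1 says "Iron containing alginate beads will be prepared for each volunteer approx. 48 hours before the test meal", so an earlier start is unlikely.

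**Volume, with k test days inside the 4-month window**

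Donation above which the limit is passed = 500 − 10 − 60k.
Total for a 450 to 500 ml donation = (460 to 510) + 60k.

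| k | Limit passed by a donation above | Total for 450–500 ml |
|---|---|---|
| 0 | 490 ml | 460–510 ml |
| 1 | 430 ml | 520–570 ml |
| 2 | 370 ml | 580–630 ml |
| 3 (A only) | 310 ml | 640–690 ml |
| 4 (A only) | 250 ml | 700–750 ml |

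**Timing**

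Let the donation be d days before screening (d ≥ 91 to escape the look-back) and Visit 3 be v days after it. At least k test days count if d + v + 7(k − 1) ≤ 120. The values of d that satisfy this are:

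| Visit 3 on day | k ≥ 1 | k ≥ 2 | k ≥ 3 (A only) | k = 4 (A only) |
|---|---|---|---|---|
| 3 | 91–117 | 91–110 | 91–103 | 91–96 |
| 7 | 91–113 | 91–106 | 91–99 | 91–92 |
| 14 | 91–106 | 91–99 | 91–92 | none |
| 21 | 91–99 | 91–92 | none | none |

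A donation 91 days before screening leaves 120 − 91 = 29 days of window (27 to 30 with calendar months). If Visit 3 is on day 30 or later, no test day counts. Then only a donation above 490 ml passes the limit, by at most 10 ml.

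**Sensitivity to the reference date.** If the 3 months were counted from Visit 3 instead, the gap would move but not close. At least one test day would count for donations 91–120 days before Visit 3, and all four for 91–99 days, since 120 − 21 = 99.

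**Check of the fix.** With a 4-month look-back and 250 ml reserved for study blood, 500 − 250 = 250 ml is left for donations. An assumed 450 to 500 ml donation inside the look-back would defer the volunteer until it is more than 120 days old. Any 4-month period that contains study blood and ends by the last test day then stays within 500 ml, provided there is no donation in between.

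**The case against.** The strongest reply is that the gap is small and rests on facts the protocol does not give. Donation volume, the interval from screening to Visit 3 and the number of men are all unstated. On the natural reading only donations aged 3 to 4 months slip through, and later starts shrink that band quickly. Fitness is also checked directly: section 6.2 measures haemoglobin, full blood count and ferritin, excludes ferritin below 15 µg/L and refers other out-of-range results to the medical advisor. Section 7 further excludes anyone whose screening results indicate unsuitability. All of this stands and limits the weight of the point. It does not remove it, because those checks do not count volume.

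The missing reference date is a lesser matter. A period described as previous is ordinarily counted from the eligibility assessment, and the transfusion criterion is worded the same way.

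Two stronger readings are tempting, and the documents do not support either.

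- A reader might take the volume to mean the donation alone, so that 500 ml given the day before screening would be accepted. That would leave the clause almost idle for any single donation of 500 ml or less, and the parallel-study criterion speaks of sampling that adds to a total. It is the less natural reading and should not be set beside the cumulative one as an equal.
- A reader might infer bias in the treatment comparison. Section 14 relates absorption to iron stores, and bead meals always precede their matched capsule meals, so a donation in between could favour the capsule day. Nothing in the protocol suggests volunteers will donate between paired days, and no size can be given. Section 11.2 plans ferritin and transferrin receptor assays on baseline samples, which could reveal a shift in iron status. The health questionnaire and test-day record sheet are annexes not shown here and may already cover donation.

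**Conclusion.** The point holds as a minor eligibility defect. Followed as written and read cumulatively, the criterion admits a donor whose last donation was 3 to 4 months before screening and who can then pass the protocol's own 500 ml limit.

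With an assumed donation of 450 to 500 ml, the total is 520 to 570 ml with one test day in the window and 580 to 630 ml with two. The figure of 700 to 750 ml should not be read as typical. It needs all four group A days at minimum spacing and, with Visit 3 on day 7 and the look-back counted from screening, a donation 91 to 92 days before screening. Group B cannot reach it.

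The conclusion rests on the cumulative reading, the assumed donation volume and a Visit 3 soon after screening. How many men would be affected cannot be derived. The documents show no harm at these volumes. The sample size, the paired test and the primary comparison are not affected.

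**What to change.** Reword the criterion in section 7 in three respects:

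- Set the look-back at 4 months before the screening blood sample.
- State that the 500 ml total counts donations plus 250 ml of study blood. The group A figure is needed for everyone because allocation is not known at screening; under section 8, "As each volunteer is recruited onto the study, the appropriately numbered envelope will be opened by the study scientist".
- Ask volunteers not to donate between screening and their last test day.

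The cost is a wording change and one agreement at Visit 2. The downside is that some male donors are screened up to about a month later (from 3 to 4 months after a donation) or put off a donation during the study. No rule on donating after the last test day is needed to close this gap, and adding one would create most of the burden.

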## **8. Study Procedures**

### Randomization

Volunteers will be assigned randomly to group A or B and they will be asked to complete up to 4 study days (4 in group A and 2 in group B). Volunteers will be unaware that if they were randomly assigned to group A it will result in completing 4 study days and that if they were assigned into group B it will result in completing 2 study days. Maintaining volunteers' unawareness will improve flexibility of pairing them for experimental days. After completing 2 study days, volunteers from group B will be contacted, thanked for their involvement and informed that their participation in the study is complete as all the required data have been collected. The PIS will contain details advising potential study participants that they will be randomly selected to take part in either two or four study days.

Randomization will be undertaken by a third party unconnected with the study using the randomization generator available at the [www.randomization.com](http://www.randomization.com) website. Randomisation will be generated for 16 sequential volunteers, and each random sequence generated will be placed in order in a sequentially numbered opaque, sealed envelope (1-16). As each volunteer is recruited onto the study, the appropriately numbered envelope will be opened by the study scientist to reveal the assignment to the group A or B. Note the study is single-blinded so the participants will be unaware to which group they will be allocated and which test meal they will be receiving on each experimental day.

### **8.1. Visit 3: First experimental day**

After recording all food and drink consumed on the day before the first experimental day (pre-test diet) in a food diary provided by the study team (Annex 12), volunteers will undergo a 10 hour overnight fast from 10:00pm and attend the CRTU at approximately 8:00 am the following morning. During the fasting period volunteers will be advised to drink water. On arrival in the CRTU a trained nurse and a scientist from the study team will be on hand to ensure that the volunteers are comfortable and relaxed. Female volunteers will also be asked whether they are menstruating and this will be noted by the study scientist. All clinical procedures described in the subsequent sections will be carried out by a fully trained nurse in the CRTU.

Prior to cannulation a CRTU nurse will take and record the volunteer's blood pressure. If the volunteer's blood pressure is  $<90/50$  or  $<95/55$  if symptomatic or  $>160/100$  three further measurements may be taken and recorded at 5 minute intervals. If the blood pressure measurement remains outside these ranges after the third measurement, the volunteer will be excluded from the study, referred to their G.P. and the study day cancelled.

If the blood pressure is within these ranges a CRTU nurse will insert an intravenous (i.v.) cannula into an appropriate peripheral vein in one of the volunteer's arms. No more than two attempts will be made to insert the cannula on any one experimental day. The cannula will remain in situ for six hours. If there are any problems with the cannula during the 6 hour sampling period either the cannula will be removed and a second cannula inserted or, if there are no more than two blood samples remaining they may be taken by venepuncture. The cannula will be flushed with sterile normal saline between blood samples to maintain patency of the cannula.

After the cannula has been appropriately sited and the first blood sample taken, the volunteers from group A and B will receive:

- Test meal 1 for all volunteers (group A and B): 200ml cola jelly prepared from 200ml cola (Coca-Cola), 10ml of commercially available

Diet Cola flavoured Drink Concentrate (Sodastream, Lakeland) and gelatine (from animal source, [name]) with the addition of ferrous gluconate (approx. 20mg +/- 2mg) in alginate beads (approx. 22.2g) followed by 200ml of diet cola drink (Coca Cola) with 3 placebo capsules (filled with 50mg commercially available dextrose acting as placebos for calcium and an iron capsules.)

Results of previous human intervention studies have shown that consumption of a cola drink has no effect on iron absorption and study participants find it a more palatable way of receiving iron doses in solution. During the six hour cannulation period volunteers will have access to a drinking water dispenser (Aquarius, UK).

Blood samples (5ml each time) will then be taken at t=0 (at baseline), then after consumption of the test meal at: 20, 40, 60, 80, 100, 120, 150, 180, 240, 300 and 360 min after the ingestion of the oral doses and collected into appropriate tubes for the preparation of serum. Blood samples will subsequently be analysed for serum iron concentrations. During the day, any adverse events and all required information will be recorded by the study scientist on the experimental day record sheet (Annex 13) and dealt with in accordance with Good Clinical Practice and NRES guidelines.

After the final blood sample has been collected, volunteers will be offered and encouraged to consume lunch which they selected from the menu during the screening visit. Lunch will be prepared by Catering Direct, University of East Anglia and will consist of: a sandwich filled with ham, cheese or tuna mayonnaise, 1 piece of fresh fruit, 1 cake bar, 1 packet of crisps, and a fruit juice drink. Selected food will be picked up from the Zest food outlet located in the main square at the University of East Anglia just before completion of a study day.

Following a minimum seven day "washout" period, the volunteers will be asked to resume their one day pre-test diet, prior to the second experimental

day (Visit 4) i.e. there will be a minimum of one week between each experimental day.

